| Consented women will be randomly assigned to the study (intervention) group or the control group.                                                                                                                                                                                                                                                                                                                                                           | 34
35                         |
| In the study group, the wound will be infiltrated in both sides with 30 ml of 0.25% bupivacaine hydrochloride mixed with adrenaline 1:200000 before wound closure.                                                                                                                                                                                                                                                                                          | 36
37                         |
| Infiltration will not be performed in the control group. Other intra- and postoperative management will be similar in both groups.                                                                                                                                                                                                                                                                                                                          | 38
39                         |
| On admission to the maternity ward, pain measurements will be recorded every 2 h for the first 6 h and then every 6 h until 24 h after admission, according to the ward protocol. Pain will be assessed by a VAS from 0 to 10, where a higher score indicates more pain.                                                                                                                                                                                    | 40
41
42                   |
| At 24 hours after surgery the women will be asked to grade their satisfaction regarding pain management after surgery on a scale of 1 to 5 where 1 = not satisfied and 5 = very satisfied.                                                                                                                                                                                                                                                                  | 43
44                         |

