| Demographic and obstetric data will be collected from the computerized sheets: woman's age, weight and height, smoking status, pre-pregnancy weight, pregnancy and birth number, number of previous caesarean sections, gestational age, background diseases, obstetric complications, use of anticoagulants, reasons for surgery, duration of surgery, type of anesthesia in surgery, and administration of analgesia at the recovery and maternity wards. | 45
46
47
48
49
50 |
| Primary outcome                                                                                                                                                                                                                                                                                                                                                                                                                                      | 51                               |
| The primary outcome will be the mean VAS scores after admission to the maternity ward.                                                                                                                                                                                                                                                                                                                                                                      | 52                               |
| Secondary outcomes will include VAS score at each time point, need for rescue opioids, duration of surgery, time from end of surgery to mobility, time from end of surgery to breastfeeding, hematoma or infection in the surgical scar, maternal satisfaction, and length of stay after surgery.                                                                                                                                                           | 53
54
55
56
57       |
| Research period                                                                                                                                                                                                                                                                                                                                                                                                                                      | 58                               |

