| Statistics                                                                                                                                                                                                                                                                                                                                                                                                                                                                                                  | 78                               |
| T-test will be used to examine differences in continuous variables between the groups. For the purpose of comparing the categorical research variables, Chi-square or the Fisher exact test for small samples we be used. Other statistical testes will be used as needed.                                                                                                                                                                                                                                         | 79
80
81                   |
| Maintaining confidentiality                                                                                                                                                                                                                                                                                                                                                                                                                                                                                 | 82                               |
| Patients' information will be stored separately in a sealed brown envelope and will not be included on the data collection sheet.                                                                                                                                                                                                                                                                                                                                                                                  | 83
84
85                   |

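### The t-test rule does not fit time to breastfeeding and time to mobility, because women without the event by discharge have no value; the primary t-test is valid but could be made slightly more precise

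*Protocol*

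**What the plan says.** The Statistics section of the protocol gives one rule for all continuous data: "T-test will be used to examine differences in continuous variables between the groups". It makes no exception for repeated readings or for times to an event. It then adds an open clause: "Other statistical testes will be used as needed".

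Under Primary outcome, "The primary outcome will be the mean VAS scores after admission to the maternity ward". The same section lists the secondary outcomes. These include VAS at each time point, the time from surgery to mobility, and "time from end of surgery to breastfeeding". Length of stay is also a secondary outcome. The Research period section ends each woman's participation at discharge home.

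Under Research plan, "pain measurements will be recorded every 2 h for the first 6 h and then every 6 h until 24 h after admission". No VAS before treatment is scheduled. The baseline data are demographic and obstetric: age, weight, height and "number of previous caesarean sections", among others.

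The Sample size section rests on a two-group difference of 1 in mean VAS with SD 3.0, 80% power and two-sided 5% alpha, giving 286 women.

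**The concern.** A t-test needs a number for every woman. For time to breastfeeding and time to mobility, a woman without the event by discharge has none. Under the stated rule she is either left out or given an arbitrary value. If she is left out, the comparison is between women who reached the event in each arm, and reaching it can itself depend on treatment. The result can even point the wrong way. If infiltration led some women to start breastfeeding late who would otherwise not have started, their long times would enter only the treated arm's mean and make that arm look slower.

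Two smaller matters follow from the same rule. The primary comparison is unadjusted although possible prognostic covariates are already being collected. And VAS at each time point becomes a series of separate tests, in which an isolated significant hour may appear by chance.

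**Working it through.** **1. The plan's own figure.** Inputs from Sample size: difference 1, SD 3.0, power 80%, two-sided alpha 5%, 1:1 allocation.
- Normal approximation: n per arm = 2 × (1.960 + 0.842)² × 3² / 1² = 141.3, rounded up to 142 (284 in total).
- Exact t solution: 142.25, rounded up to 143 per arm, so 286. This matches the protocol.
- Power at 143 per arm: 80.5% (normal) or 80.2% (t).

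**2. Time-to outcomes.** No arithmetic is possible, because the protocol does not say how many women are expected to be discharged without breastfeeding or mobilising. Side by side: Statistics prescribes a t-test for continuous variables; Primary outcome lists two times measured from the end of surgery; Research period stops observation at discharge. Where the event has not happened by then, only a lower bound on the time is known. A t-test cannot use a lower bound; a survival analysis can.

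**3. Primary test.** Does a t-test on one mean VAS per woman hold its level when the number of readings varies? In 20,000 simulated trials under no effect (143 per arm, assumed between-reading correlation 0.5, 3 to 7 readings per woman), the rejection rate was 5.0%. There is no inflation.

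**4. Gain from adjustment.** If the covariates have multiple correlation r with the outcome (assumed; the protocol gives none), the residual SD is 3.0 × √(1 − r²), and power = Φ(1 / (SD × √(2/143)) − 1.960).

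| r | Power at 143 per arm | n per arm for 80% (normal) |
|---|---|---|
| 0 | 80.5% | 142 |
| 0.1 | 80.9% | 140 |
| 0.2 | 82.0% | 136 |
| 0.3 | 84.0% | 129 |

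The gain is 0.4 to 3.5 percentage points for r of 0.1 to 0.3.

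**5. Time-point tests.** The schedule gives readings at 2, 4, 6, 12, 18 and 24 h, which is 6, or 7 if one is also taken at admission. Assume each is tested at 5%. If independent, the chance of at least one false positive is 1 − 0.95⁶ = 26.5% or 1 − 0.95⁷ = 30.2%. With equally correlated readings (correlations assumed; 400,000 simulated sets):

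| Correlation | 6 readings | 7 readings |
|---|---|---|
| 0.3 | 24.2% | 27.2% |
| 0.5 | 20.6% | 22.9% |
| 0.7 | 16.5% | 17.8% |

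**The case against.** **The protocol never says that women without the event are dropped, and it allows other tests.** True. The exclusion follows from applying the stated rule; it is not written down. But the open clause names neither a test nor the circumstance that would trigger it, so it does not correct the mismatch and leaves the choice free to follow the data. A separate analysis plan could add detail, but for these outcomes it would have to depart from the test the protocol names. What stands is that the size of the problem is unknown, and that for mobility it may be small, since nothing suggests many women go home without having mobilised.

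**Censoring at discharge has its own weakness.** It does. Length of stay is itself an outcome, so discharge may be related to treatment or recovery, and women who do not intend to breastfeed are not ordinary censored cases. This is a reason to report the proportion with the event by discharge as well, not to keep the t-test.

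**Covariate adjustment is a preference.** In part. The unadjusted comparison is valid and is what the trial was powered for. There is no baseline VAS, and the planning SD of 3.0 already exceeds the 0.1 to 2.7 quoted from the literature, so no shortfall in precision is shown. Adjustment is a cheap improvement, not the repair of an error.

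**Multiplicity over secondary time points belongs in an analysis plan.** This stands. The time points are plainly secondary, and the protocol's 5% appears only in the sample-size calculation. The absence of a multiplicity rule is therefore not counted as a fault.

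**Stronger readings that a reader might infer.** One is that the primary test is inflated because the VAS series is repeated. That would follow if all readings were pooled as independent rows: type I error would then be 21.5% to 39.0% for 6 or 7 readings at correlations of 0.3 to 0.7. The protocol does not propose this. The outcome is a mean, the sample size counts women, and one mean per woman is the natural reading. Another is that the t-test rule drops women from the primary analysis. It does not do so as such: a woman with some readings still has a mean.

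**Conclusion.** The stated t-test rule is unsuitable for time to breastfeeding and time to mobility. Followed literally, it compares subsets selected after randomisation. The bias cannot be quantified because the share without the event is not given; breastfeeding is the main concern.

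The primary t-test on one mean VAS per woman is valid at 5%, and 286 reproduces. Adjustment offers a modest gain, from about 80.5% power to between 80.9% and 84.0%, resting on an assumed r of 0.1 to 0.3.

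The time-point tests carry a 16.5% to 27.2% chance of at least one false positive over 6 or 7 readings at assumed correlations of 0.7 to 0.3 (26.5% or 30.2% if independent). This calls for a label, not a correction to the trial's main claim.

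**What to change.** - **Time to breastfeeding and time to mobility:** include all randomised women; compare by Kaplan-Meier with log-rank or Cox, censoring at discharge; report by arm the proportion with the event by discharge. Name these methods in place of the open clause.
- **Primary outcome:** state that it is one mean VAS per woman, and compare it in a linear model with arm plus number of previous caesareans, age and BMI, fixed in advance. The estimand, a difference in mean VAS, is unchanged.
- **VAS at each time point:** label as descriptive, with estimates and confidence intervals. Do not make reporting conditional on an arm-by-time test, because a benefit that is constant over time produces no interaction and would go unreported. State whether there are 6 or 7 readings.

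The cost is wording only. BMI follows from the weight and height already recorded, and discharge is already the end of participation, so no new data are needed. The remaining limitation is that censoring may be related to length of stay, which the event proportions help the reader to judge.
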